### 2.4. Sample Size Calculation

Sample size was estimated a priori using G*Power 3.1 [37]. Maximal voluntary contraction pressure (mmHg), assessed by manometric perineometry, was selected as the single primary outcome because it provides an objective and quantitative measure of PFM strength and is the outcome most directly related to the primary study hypothesis.

Previous randomized controlled trials involving women with UI have shown that vaginal manometric measures of PFM strength and endurance are responsive to exercise-based interventions incorporating specific or voluntary PFM contractions. In particular, Gonzaga et al. [38] reported improvements in manometric measures of PFM strength and endurance following PFM training and Pilates exercise performed with voluntary PFM contraction in postmenopausal women with UI. However, because previous studies are characterized by relatively small sample sizes and heterogeneous interventions and do not provide either a directly applicable standardized effect size or an established clinically important difference for the planned group-by-time comparison, Cohen’s f = 0.24 was selected as a conservative a priori planning assumption rather than an empirically derived effect estimate [39,40].

The calculation was based on a repeated-measures ANOVA model (within-between interaction; four groups; three time points: T0, T1, T2; two-tailed α = 0.05; statistical power = 1 − β = 0.80; assumed correlation among repeated measures r = 0.50; and Cohen’s f = 0.24). Under these assumptions, the minimum analytical sample required was estimated at 96 participants. Nevertheless, the planned recruitment target was set at 120 participants (30 per group). This target exceeds the minimum sample size required by the formal power calculation and was selected to preserve balanced allocation across the four intervention groups, accommodate anticipated attrition and incomplete follow-up data, and improve the precision and stability of the estimated longitudinal treatment effects obtained from the planned linear mixed-effects models (LMM). The anticipated attrition rate was conservatively estimated at 20%, based on participant retention reported in comparable randomized exercise-based interventions involving older women with UI [7,41,42].

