### 2.7. Study Variables

Outcome measures will assess physical/functional and psychological domains. Sociodemographic and clinical variables (age, anthropometrics, obstetric history [number of pregnancies and vaginal deliveries], menopause onset, comorbidities, medication use, and lifestyle factors) will be collected at baseline. Current medications potentially affecting urinary function (e.g., diuretics and antihypertensive medications) will also be recorded. All outcome measures will be assessed at baseline, post-intervention (18 weeks), and at 6-month follow-up.

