#### 2.7.2. Secondary Outcome Measures

PFM function

PFM function will be evaluated using the PERFECT assessment scheme, developed and validated by Laycock and Jerwood [55]. The following components will be assessed according to standardized procedures: Power (maximal voluntary contraction graded 0–5 using the modified Oxford scale), Endurance (duration of a sustained maximal voluntary contraction, up to 10 s), Repetitions (number of repeated sustained contractions at the same intensity, up to 10), and Fast contractions (number of rapid 1 s contractions with full relaxation between efforts, up to 10). All digital palpation assessments will be performed by the same trained physiotherapist using a standardized assessment protocol, thereby eliminating inter-rater variability. The individual PERFECT components (Power, Endurance, Repetitions, and Fast contractions) will be recorded and analysed separately as secondary outcomes. No aggregate or total PERFECT score will be calculated.

Objective assessment of PFM activation will be performed using intracavitary electromyography (iEMG), a valid and reliable method for assessing PFM neuromuscular activation in women with PF dysfunction, including UI [56]. Maximum and mean voluntary contraction amplitudes will be recorded using the NeuroTrac^®^ MyoPlus2 Pro system (Verity Medical Ltd., Hampshire, UK) with a vaginal intracavitary electrode and a surface reference electrode. To improve between-session comparability and reduce the influence of electrode placement and reinsertion variability, iEMG amplitudes will be normalized within each assessment session. Specifically, EMG activity recorded during each contraction will be expressed as a percentage of the maximum voluntary contraction obtained during the same assessment session (%MVC). Absolute amplitudes in µV will be retained for descriptive purposes, whereas normalized %MVC values will be used for longitudinal comparisons across baseline, post-intervention, and follow-up assessments.

B.Urinary incontinence patterns and impact

UI-related symptoms and voiding patterns will be assessed using a 3-day voiding diary, a widely accepted and validated clinical tool that captures urinary frequency, leakage episodes, and symptom severity in daily life contexts [57].

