UI severity and its impact on quality of life will be assessed using the International Consultation on Incontinence Questionnaire–Short Form (ICIQ-SF). The ICIQ-SF is a validated and widely used instrument in older adults. Total scores range from 0 to 21, with higher scores indicating greater symptom severity [35].

C.Abdominal muscle function

Abdominal muscle morphology and activation will be assessed using ultrasound imaging to evaluate inter-recti distance and transversus abdominis (TrA) activation. Measurements will be performed with a portable ultrasound device (General Electric Logiq E V2) equipped with a linear transducer, and values will be expressed in millimeters (mm). Participants will be positioned in a supine position with the LL flexed to minimize lumbar lordosis and abdominal wall tension. Inter-recti distance will be measured with the transducer placed transversely at standardized locations 1 cm above and 1 cm below the umbilicus. Measurements will be obtained under two conditions: at rest and during forced exhalation, corresponding to the activation phase of diaphragmatic breathing. The difference between conditions will be used to quantify changes in rectus abdominis separation.

Bilateral TrA activation will be assessed with the transducer positioned transversely along the mid-axillary line, midway between the iliac crest and the costal margin. Measurements will be performed at rest and during forced exhalation, and changes in muscle thickness between conditions will be used as an indicator of TrA activation. Ultrasound imaging has been shown to be a valid and reliable method for assessing abdominal muscle morphology and activation patterns in clinical and research settings [58,59].

D.Gait and aerobic capacity

Gait speed will be assessed using the 4-Meter Walk Test (4MWT) at usual and maximal walking speeds. To minimize acceleration effects, participants will start walking 0.5 m before the first marker and continue walking 0.5 m beyond the end marker. The time required to complete the central 4 m will be recorded, and gait speed will be calculated in meters per second (m/s) [60]. The 4MWT is a widely used and validated measure of functional mobility in older adults, demonstrating good reliability and strong clinical relevance [61].

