To formally evaluate the dose–response pattern hypothesized in H2, a pre-specified linear trend analysis will be conducted using orthogonal polynomial contrasts applied to the group factor within the LMM framework. The four groups will be assigned contrast weights reflecting the sequential addition of intervention components and their expected incremental dose: Control = −3, EX = −1, EXVERB = +1, EXVERBPSY = +3. These weights correspond to the standard orthogonal polynomial contrast coefficients for four equally spaced ordered groups [40]. This analysis therefore assumes equally spaced incremental treatment effects across the four study arms and is intended to test the prespecified hypothesis of a monotonic additive dose–response trend, rather than implying that the additional intervention components are biologically or clinically equivalent. A statistically significant positive linear contrast at T1 will be interpreted as confirmatory evidence supporting a monotonic dose–response relationship across the additive intervention arms, consistent with H2. Results at T2 will be interpreted as exploratory, addressing the persistence of the dose–response pattern at follow-up. The effect size for the linear trend will be reported as r^2^contrast = Fcontrast/(Fcontrast + dferror). This analysis will be conducted for the primary endpoint and, as exploratory analyses, for the pre-specified secondary outcomes.

All secondary and exploratory outcomes will be analysed using the same LMM framework. Sequential Holm–Bonferroni correction will be applied across the five pre-specified pairwise contrasts for each secondary outcome, consistent with the primary analysis. However, no global family-wise error rate correction will be applied across secondary outcomes. Results will be presented with adjusted *p*-values for the planes pairwise comparisons, Cohen’s d effect sizes with 95% confidence intervals, and η^2^p for global F-tests. Findings from the prespecified secondary outcomes will be interpreted as supportive rather than confirmatory, whereas exploratory outcomes will be interpreted as hypothesis-generating.

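### The protocol sets out to evaluate inter-recti distance, but the only value it puts to use is a same-visit rest-versus-exhalation difference, which does not follow separation over time

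*Protocol article*

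**What the plan says.** Section 2.7.2 C of the protocol article opens with its purpose: "Abdominal muscle morphology and activation will be assessed using ultrasound imaging to evaluate inter-recti distance and transversus abdominis (TrA) activation". Inter-recti distance is read in millimetres at two sites, 1 cm above and 1 cm below the umbilicus. On the conditions it says: "Measurements will be obtained under two conditions: at rest and during forced exhalation, corresponding to the activation phase of diaphragmatic breathing". The next sentence is the only one that assigns the inter-recti readings a use: "The difference between conditions will be used to quantify changes in rectus abdominis separation". The direction of subtraction is not given.

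Two general statements carry this value into the analysis. Section 2.7: "All outcome measures will be assessed at baseline, post-intervention (18 weeks), and at 6-month follow-up". Section 2.8.1: "All secondary and exploratory outcomes will be analysed using the same LMM framework". On the text, the inter-recti quantity that enters the group-by-time model is thus the same-visit difference. Neither resting distance nor exhalation distance is named as an analysed variable.

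**The concern.** A rest-to-exhalation difference says how far the gap moves during one manoeuvre. It does not say how wide the gap is. If the trial wants to know whether training alters separation, a group-by-time contrast on this difference can miss a real alteration. It can also report a change in separation when only the response to exhalation has altered.

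The second risk is relevant to this design. Diaphragmatic breathing is part of the exercise programme (Section 2.6.8). The EXVERB and EXVERBPSY arms are also taught to coordinate pelvic floor contraction with it (Section 2.6.9), and control education touches on breathing control (Section 2.6). The arms may therefore come to perform the test manoeuvre differently. That is a legitimate finding about activation, but it would be mislabelled if reported as a change in separation.

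**Working it through.** The documents give no inter-recti values, so there is no stated figure to reproduce. The core of the point is algebra; every millimetre value, SD and correlation below is an assumption used for illustration.

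**Identity.** Let R and E be the distances at rest and on forced exhalation, with D = R − E at each visit. From T0 to T1:

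D1 − D0 = (R1 − R0) − (E1 − E0) = dR − dE.

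If dR = dE, the change in D is zero. Subtracting the other way round only flips the sign.

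**Illustrations**, assuming R0 = 20 mm and E0 = 17 mm, so D0 = 3 mm:

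| dR (mm) | dE (mm) | D1 (mm) | Change in D (mm) |
|---|---|---|---|
| −4 | −4 | 3 | 0 |
| −4 | −3 | 2 | −1 |
| −4 | −2 | 1 | −2 |
| −4 | −5 | 4 | +1 |
| 0 | −2 | 5 | +2 |

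In the first four rows the resting gap narrows by the same 4 mm, yet the score falls, stays level or rises. In the last row the resting gap is unchanged and the score moves by 2 mm.

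**How much is lost.** Write dE = s × dR. The change in D is then (1 − s) × dR. At s = 0 nothing is lost, at s = 0.5 half, at s = 1 all. Above 1 the sign reverses. The documents say nothing about s.

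**What this could mean for power (illustration only).** Section 2.4 plans 30 per group; with its 20% attrition, 30 × 0.8 = 24 per group. Assume a 4 mm between-group narrowing at rest, an SD of change of 4, 6 or 8 mm in each condition, and a correlation of 0.8 between the two changes. The SD of the change in D is then SD × √(2 × (1 − 0.8)) = 0.632 × SD. Power is approximately Φ(δ / (SD × √(2/24)) − 1.96). For resting distance with SD 4: 4 / (4 × 0.2887) = 3.46, and Φ(1.50) = 0.93.

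| SD of change (mm) | Power, resting distance, 4 mm | Power, D, equal shifts | Power, D, dE = −3 | Power, D, dE = −2 |
|---|---|---|---|---|
| 4 | 0.93 | 0.05 | 0.28 | 0.78 |
| 6 | 0.64 | 0.05 | 0.15 | 0.45 |
| 8 | 0.41 | 0.05 | 0.10 | 0.28 |

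With equal shifts the rejection rate is just alpha, whatever the SD or sample size. With unequal shifts the result depends on an input the documents do not supply.

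**Comparison within Section 2.7.2.** For transversus abdominis, the between-condition thickness change is presented as an indicator of activation, so score and construct match. For intracavitary EMG the section says what happens to both the raw and the derived values: "Absolute amplitudes in µV will be retained for descriptive purposes, whereas normalized %MVC values will be used for longitudinal comparisons". The inter-recti text has no such sentence, and it ties a response score to separation.

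**The case against.** The strongest defence is that the sentence refers to the acute change from rest to exhalation. It directly follows the description of the two conditions, the transversus abdominis paragraph has the same form, and the subsection is headed as muscle function. On that reading the difference is a valid score, and an arm difference caused by cued activation is the score doing its job. This stands as a fair reading. It does not remove the point: the plan then follows an activation response and names no analysed measure of the separation it says it evaluates.

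A second defence is that an article may leave lists of analysed variables to a fuller document. That would answer a bare omission. Here the article states which value will be used and for what.

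Two stronger readings are tempting and should not be drawn. A reader might infer that the plan excludes resting distance from analysis. It does not: both readings are taken, and nothing bars their use. A reader might also infer that a real narrowing will cancel, or that some stated share of it will be lost, or that the difference score has a particular low reliability. Cancellation is complete only for the part common to both conditions, and any percentage or reliability would merely restate assumed inputs. Nor is the difference always the noisier quantity: under the correlation of 0.8 assumed above, its change has a smaller SD than the change at rest.

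Finally, no hypothesis from H1 to H4 concerns resting separation. That is true, and it limits the weight of the point.

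**Conclusion.** The point holds as a mismatch between what is to be evaluated and the value named for it. That the change in the score equals dR − dE is an identity and needs no assumption. The consequence is that shared narrowing or widening is invisible to the score, and that the score can change with resting separation constant. How large this would be in the trial is unknown.

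The importance is minor. One secondary outcome is affected, Section 2.8.1 treats such outcomes as supporting evidence only, and the raw readings are kept. The primary endpoint, the sample size and the contrasts on the primary endpoint are unaffected.

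**What to change.** In Section 2.7.2 C, name resting inter-recti distance (mm), 1 cm above and 1 cm below the umbilicus, as an analysed secondary outcome for separation in the mixed model. Keep the difference, define it as rest minus exhalation, and describe it as a measure of activation response.

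No new measurement is needed, and settling this before analysis avoids a later choice between two scores that can point in opposite directions. The cost is additional supportive testing. If the two sites are analysed separately, the five planned contrasts at T1 and T2 add 2 × 5 × 2 = 20 comparisons. Under Section 2.8.1 these are Holm-corrected within each outcome and time point, but not across secondary outcomes.

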#### 2.7.3. Adherence, Safety and Co-Interventions

Before each assessment session, participants will be screened for any new medical conditions or contraindications that could compromise the safe performance of the assessments. Maximal jump tests (CMJ and ABK) will only be performed when participants are considered clinically fit by the supervising physiotherapist, as CMJ has been demonstrated to be a safe and valid assessment of LL muscle power in community-dwelling older adults [79,80].

Any assessment or exercise session will be immediately interrupted if the participant develops chest pain, severe dyspnea, dizziness, syncope, acute musculoskeletal pain, neurological symptoms, or any other clinical sign judged by the supervising physiotherapist to compromise safe participation. Participants may also stop any assessment or exercise session at their own request.

Adherence to the intervention will be systematically monitored throughout the study period using a structured session-by-session attendance register. A minimum attendance threshold of 80% of scheduled sessions will be required to classify a participant as adherent, consistent with criteria applied in comparable exercise-based trials in older adults. Reasons for any missed session will be documented by the supervising physiotherapist to distinguish between voluntary withdrawal, health-related absence, and logistical barriers, thereby enabling a more nuanced interpretation of adherence patterns across groups and time points.

AE will be recorded prospectively using a standardized monitoring log completed by the supervising physiotherapist at the end of each session. AE will be defined as any unintended sign, symptom, or condition occurring during or within 48 h of a session, regardless of causal attribution to the intervention. These will include musculoskeletal complaints (e.g., joint pain, muscle strain), cardiovascular symptoms (e.g., dizziness, chest discomfort, unusual dyspnea), PF-related symptoms (e.g., increased urinary leakage or pelvic pain following exercise), and any fall or near-fall event occurring within the study context. AE will be classified by severity (mild, moderate, severe) and by relationship to the intervention (unrelated, possibly related, probably related, definitely related). Serious adverse events (SAE) will be reported immediately to the principal investigator and to the Ethics Committee of the Catholic University of Valencia in accordance with applicable regulatory requirements. Participants experiencing an SAE will be temporarily or permanently withdrawn from the intervention at the discretion of the supervising clinician and will continue to be included in the intention-to-treat analysis wherever feasible. Participants who are temporarily withdrawn may resume participation once symptoms have resolved and, when clinically indicated, after reassessment by the supervising physiotherapist and medical clearance.

Co-interventions with the potential to influence study outcomes will be monitored throughout the intervention and follow-up periods using a structured self-reported log completed by participants at each assessment time point. At the post-intervention assessment (T1), participants will report any relevant co-interventions occurring during the intervention period (T0–T1), whereas at the follow-up assessment (T2), they will report co-interventions occurring during the follow-up period (T1–T2). Co-interventions of interest will include any physiotherapy treatment targeting the LL, spine, or PF; formal PFM rehabilitation programmes delivered outside the study context; and any initiation, discontinuation, or modification of pharmacological treatments known to affect urinary function, neuromuscular performance, or fall risk (e.g., anticholinergics, alpha-blockers, diuretics, benzodiazepines, or antihypertensives). The occurrence and nature of co-interventions will be reported descriptively and considered as potential confounding variables during data interpretation, particularly in cases where marked between-group imbalances are identified.

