### 2.6. Interventions

The intervention will consist of 36 supervised multicomponent exercise sessions, and, for one study arm, six structured PSY sessions delivered over 18 weeks. Exercise sessions will be conducted twice weekly on non-consecutive days (55–60 min/session) and will target balance, power, strength, aerobic capacity, agility/coordination, and flexibility with progressive intensity. Sessions will be led by a physiotherapist specialized in geriatrics (five years of experience), with methodological oversight by a research supervisor using a standardized supervision checklist to ensure fidelity and safety.

Participants will be allocated to one of the four groups:-G1: (EX) PMT only.-G2: (EXVERB) EX plus verbal cues to facilitate PFM contractions during balance and strength exercises.-G3: (EXVERBPSY) EXVERB plus six structured PSY sessions delivered during the intervention period.-G4: (Control Group) Participants will receive four educational sessions (one per month, 45–60 min per session) focused on the prevention of geriatric syndromes and instructions to maintain their usual physical activity. The sessions will address topics related to breathing control, postural control, balance and fall prevention, and pelvic floor (PF) health. After study completion, control participants will be offered the opportunity to receive the intervention components not undertaken during the initial study phase.

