### 2.8. Statistical Analysis

#### 2.8.1. Data Analysis Plan

All statistical analyses will be performed using IBM SPSS Statistics (version 29) and R (version 4.3, R Core Team, 2024). All tests will be two-tailed, with statistical significance set at *p* ≤ 0.05. Descriptive statistics (means, standard deviations, frequencies, and percentages, as appropriate) will be reported for all sociodemographic, clinical, and outcome variables at each assessment time point.

Analyses will follow the intention-to-treat (ITT) principle, including all randomized participants in the groups to which they were originally allocated, regardless of intervention adherence or study completion. As a sensitivity analysis, a per-protocol analysis will also be conducted including only participants who attended ≥ 80% of scheduled sessions and completed all assessment time points.

The primary analysis will be conducted using likelihood-based estimation within the cLDA framework, which incorporates all available observations under the missing-at-random (MAR) assumption. Missing data patterns, including Little’s MCAR test, will be explored descriptively but will not determine the primary analytical approach. Multiple imputation by chained equations (MICE) will be performed as a pre-specified sensitivity analysis to evaluate the robustness of the primary findings.

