### Limitations

The present protocol has several limitations that should be acknowledged.

(i)The active intervention groups receive substantially more participant–therapist contact than the educational control group (36 supervised exercise sessions vs. four monthly educational sessions), which may contribute to observed between-group differences beyond the specific intervention components. The control condition was intentionally designed to reflect realistic community practice rather than an attention-matched control, and the educational sessions provided to this group, covering healthy ageing, fall prevention, and pelvic floor health, may have improved participants’ knowledge and health-related behaviours, potentially affecting some outcomes, although they were not expected to produce the specific physiological adaptations associated with supervised exercise.(ii)The sample size was calculated exclusively based on the primary endpoint (maximal voluntary contraction pressure assessed by manometric perineometry). Accordingly, this trial may not be adequately powered to detect smaller between-group differences in secondary outcomes or in the pre-specified subgroup analyses according to UI subtype. These analyses should therefore be considered exploratory and hypothesis-generating.(iii)The study is restricted to community-dwelling older women, limiting generalizability to institutionalised populations or men.(iv)Intracavitary EMG amplitudes will be normalised to within-session MVC (%MVC) to reduce inter-session variability; however, this approach does not fully eliminate variability arising from training-induced changes in MVC neuromuscular characteristics, and longitudinal iEMG findings should be interpreted with appropriate caution.(v)Movement velocity during power training sessions will not be directly monitored; although the maximum intended velocity instruction and RPE-based intensity targets provide operational control of the training stimulus, confirmation that participants trained within the intended velocity range on a repetition-by-repetition basis is not possible.(vi)Falls and near-falls will not be prospectively recorded during the intervention or follow-up period; future trials in this population should be adequately powered to include fall incidence as a primary endpoint alongside functional and psychological outcomes.(vii)The a priori sample size was estimated using a repeated-measures ANOVA approximation in G*Power 3.1 [43], as dedicated LMM-specific power calculators are not readily available; under the assumed compound-symmetry covariance structure this approximation is considered conservative and reproducible, but represents a minor methodological limitation of the a priori calculation.

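### Adverse events are defined by proximity to a session, so AE-eligible time is about nine times longer in the exercise arms than in Control (5.6 to 11.5 by reading); the 80% per-protocol rule has a smaller version of the same fault

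*Protocol article*

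**What the plan says.** **Sessions by arm.** Section 2.6 of the protocol article: "The intervention will consist of 36 supervised multicomponent exercise sessions, and, for one study arm, six structured PSY sessions delivered over 18 weeks". For Control: "Participants will receive four educational sessions (one per month, 45–60 min per session". Limitations (i) repeats the contrast ("36 supervised exercise sessions vs. four monthly educational sessions"), but only as a possible cause of differences in outcomes. Section 2.6.2 adds familiarization sessions: two in EX, four in EXVERB and EXVERBPSY, none in Control. Section 2.6.11 provides no supervised sessions during the six-month follow-up.

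**Adverse events.** Section 2.7.3: "AE will be defined as any unintended sign, symptom, or condition occurring during or within 48 h of a session, regardless of causal attribution". The log is filled in by the supervising physiotherapist when each session ends. The listed events include "any fall or near-fall event occurring within the study context". Section 2.6.1 says more broadly that AEs are logged over the whole intervention. Limitations (vi) says: "Falls and near-falls will not be prospectively recorded during the intervention or follow-up period".

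**Per-protocol set.** Section 2.8.1 describes a sensitivity analysis "including only participants who attended ≥ 80% of scheduled sessions and completed all assessment time points". Section 2.7.3 uses the same 80% attendance threshold to classify a participant as adherent. Neither section gives an arm-specific or component-specific rule.

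**The concern.** Both rules use the session as their unit, and the number of sessions differs sharply by arm.

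For harms, the definition decides what counts as an AE as well as how it is logged. The same knee pain or dizziness, at the same true rate, qualifies on most days in an exercise arm and on very few days in Control. A table of AEs by arm would then mix any effect of exercise with the difference in observation time. A log completed at the end of a session can also pick up the following 48 hours only at the next contact, which in Control is about a month later.

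For the per-protocol set, a percentage threshold on four sessions has no room for a single absence. Controls are therefore selected more strictly than exercisers. In EXVERBPSY the rule does not secure exposure to the component that distinguishes that arm from EXVERB.

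**Working it through.** **Session count reproduced.** 18 weeks × 2 per week = 36, as section 2.6 states. The intervention lasts 18 × 7 = 126 days.

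**AE-eligible time** = sessions × 48 h, assuming full attendance and windows that do not overlap. ("Exercise sessions will be conducted twice weekly on non-consecutive days (55–60 min/session" makes overlap negligible for the exercise sessions.)

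| Reading | Exercise arm | Control | Ratio |
|---|---|---|---|
| Programme sessions only | 36 × 2 = 72 days (57% of 126) | 4 × 2 = 8 days (6%) | 36/4 = 9.0 |
| Three assessment visits also count, all arms | 39 windows | 7 windows | 39/7 = 5.6 |
| EX with familiarization | 38 windows | 4 | 9.5 |
| EXVERB with familiarization | 40 windows | 4 | 10.0 |
| EXVERBPSY with psychoeducation | 42 windows | 4 | 10.5 |
| EXVERBPSY with psychoeducation and familiarization | 46 windows | 4 | 11.5 |

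Illustration, assuming one true event per woman per 126 days in every arm and 30 women per arm: recorded events would be 30 × 72/126 = 17.1 in an exercise arm and 30 × 8/126 = 1.9 in Control, with no real difference.

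In follow-up there are no programme sessions. The only possible windows are the tail of the last session and, if assessment visits count, those around T1 and T2.

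**Per-protocol minimum** = 0.80 × scheduled sessions, rounded up.
- Control: 0.80 × 4 = 3.2, so 4 of 4 (3 of 4 is 75% and fails).
- 36 sessions: 28.8, so 29; seven may be missed.
- 42 sessions (exercise plus psychoeducation): 33.6, so 34; eight may be missed.
- An EXVERBPSY woman with every exercise session and no psychoeducation scores 36/36 = 100%, or 36/42 = 86%. She qualifies on either denominator.

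**Share qualifying on attendance.** The protocol gives no per-session attendance probability, so the mean m is assumed, equal in all arms. With independent sessions the count is binomial: m⁴ in Control, and P(X ≥ 29 of 36) in the exercise arms. With within-person correlation ρ it is beta-binomial, with a = m(1/ρ − 1) and b = (1 − m)(1/ρ − 1). Example for Control at m = 0.85, ρ = 0.1: a = 7.65, b = 1.35, and P(4 of 4) = (7.65 × 8.65 × 9.65 × 10.65)/(9 × 10 × 11 × 12) = 0.57.

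| m | ρ | Control, 4 of 4 | Exercise, ≥29 of 36 | Control if 3 of 4 sufficed |
|---|---|---|---|---|
| 0.85 | 0 | 52% | 84% | 89% |
| 0.85 | 0.1 | 57% | 73% | 86% |
| 0.85 | 0.3 | 65% | 73% | 84% |
| 0.90 | 0 | 66% | 98% | 95% |
| 0.90 | 0.1 | 70% | 85% | 92% |
| 0.90 | 0.3 | 76% | 83% | 90% |

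At m = 0.85 the gap runs from 84 − 52 = 32 points with independent sessions to about 8 points at ρ = 0.3.

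**The case against.** - **No between-arm AE test is planned.** This is correct. Section 2.8.1 specifies none, and 2.7.3 describes a safety log with attribution categories. A reader might infer that the plan contains a biased harm analysis; it does not. The distortion arises once counts are set side by side by arm.
- **Other channels exist.** Section 2.6.1 covers the whole intervention, 2.7.3 screens for new conditions before each assessment, and the co-intervention log covers T0–T1 and T1–T2 in all arms. So it goes too far to say that every event outside the windows is lost. None of these, however, redefines an AE or says how one outside a window would be recorded.
- **Nine is not the only ratio.** This stands, hence the range of 5.6 to 11.5. The imbalance persists under every reading.
- **The statements on falls may not truly conflict.** Section 2.7.3 limits itself to the study context, and Limitations (vi) goes on to fall incidence as an endpoint for future trials. It probably means that falls are not an outcome. That makes this mainly a clash of wording, but the literal texts disagree.
- **The per-protocol set is only a sensitivity analysis.** This stands. It would be wrong to say that the EXVERBPSY versus EXVERB contrast is broken: the primary contrast is intention-to-treat. The article also leaves the denominator open, and a component-by-component reading would exclude the woman with no psychoeducation. The 32-point gap depends on independent sessions, and clustering within women shrinks it.

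**Conclusion.** The point holds with these limits. As written, the AE definition gives the exercise arms about nine times the AE-eligible time of Control (5.6 to 11.5 by reading) and leaves the six-month follow-up almost uncovered. AE counts by arm would be distorted by ascertainment. This rests on full attendance and on taking the 48-hour definition literally. Section 2.6.1 and Limitations (vi) need reconciling with 2.7.3.

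The per-protocol fault is secondary. Control must attend 4 of 4 against 29 of 36. At an assumed mean attendance of 0.85, about 52–65% of controls would qualify against 72–84% of exercisers, over within-person correlations from 0 to 0.3. The true attendance and correlation are unknown. The primary analysis does not depend on either rule.

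**What to change.** **Adverse events.** In 2.7.3, define the AE period by calendar time, randomisation to T1 and T1 to T2, identically in all arms. Ask every participant the same AE and fall questions at T1 and T2, alongside the existing co-intervention log. Keep the session log, and report session-linked events separately for the exercise arms. Align 2.6.1 and Limitations (vi) with this, stating which falls are recorded and that fall incidence is not an outcome, if that is what is meant.

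**Per-protocol set.** Apply the 80% threshold separately to exercise (29 of 36) and, in EXVERBPSY, to psychoeducation (0.80 × 6 = 4.8, so 5 of 6). Accept at least 3 of 4 in Control.

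**Cost.** A few added questions and some rewording, plus an ethics amendment under section 3.2. Recall over months is less exact than a session log. Data collection was planned from January 2026, so women already assessed may lack the new items. With only four sessions no threshold matches 80% exactly: 3 of 4 is somewhat lenient (84–89% of controls qualifying at mean attendance 0.85, against 72–84% of exercisers), but it no longer demands perfect attendance in one arm alone.
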